### 3. TRIAL POPULATION

Participants will be recruited on a voluntary basis from a cohort of individuals with average LDL level between 100-190 mg/dL ( $100 \text{ mg/dL} \leq \text{LDL} < 190 \text{ mg/dL}$ ). The study will be conducted at several hospitals in Sri Lanka. Informed written consent will be obtained from all study participants. Details of the inclusion and exclusion criteria are given below.

#### 3.1 Inclusion Criteria

Subjects will be eligible if they meet all the following inclusion criteria:

- Age between 18-70 years
- LDL level; between 100 and 190 mg/dL ( $100 \text{ mg/dL} \leq \text{LDL} < 190 \text{ mg/dL}$ )

#### 3.2 Exclusion Criteria

Subjects who meet any of the following exclusion criteria are not to be enrolled in the study.

- Participants with an allergy to cinnamon
- Already on cinnamon or any other nutritional / herbal / ayurvedic supplements.
- Lactation, pregnancy or unwillingness to use an effective form of birth control for women of childbearing years
- Any form of malignancy at present or in the past
- Blood dyscrasias
- Estimated Glomerular Filtration Rate (eGFR)  $< 60 \text{ ml/min}$
- Patients with diagnosed alcoholic liver disease (ALD), decompensated cirrhosis or abnormal baseline liver function tests (ALT, AST - Above three times the upper limit of normal)
- Patients with cardiac, liver, renal or respiratory failure (Annexure 01)
- Patients with ASCVD or any other major critical illnesses.
- Any condition that, in the opinion of the primary investigator, would contraindicate the patient's participation

- Currently on statins or any other lipid lowering drug or if investigator decides that the participant is in need of an immediate lipid lowering therapy (statin) based on clinical judgement.
- Participant with triglycerides level  $\geq 300$  mg/dL
- Participants with a history of epilepsy and/or on anti-epileptic drugs

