### 4.4 Visit details

#### 4.4.1 Screening

Adult volunteers aged between 18 - 70 years who are not on lipid lowering drugs will be screened for eligibility criteria after obtaining their consent. Informed consent will be obtained from all the participants for participation in the study. The participants will be required to sign or print thumb impression (those unable to sign). Those who consent will be screened for eligibility into the study with Screening Form. Individuals with average serum LDL level 100-190mg/dL will be recruited to the study considering other exclusion criteria and a unique study identifier will be given, and baseline data collection will be administered. All women of child-bearing potential must have a

negative highly sensitive pregnancy test 7 days or fewer before starting medication and must use a highly effective method of contraception throughout their participation in the study. Laboratory investigations will be conducted for the participants who are willing to participate in the study. Lipid profiles done up to 7 days prior to screening visit will be considered to determine the eligibility at screening and as baseline lipid parameters.

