#### Steps to be followed at screening (Visit 1)

- Assess the potential participant's interest and eligibility for the trial.
- Discuss the trial with the participant, including using the participant information sheet, and obtain signed informed consent. This can also be done before the screening visit.
- Perform pregnancy test & contraception review if applicable
- Collect demographic information.
- Collect information on medical history
- Measure height, weight, WC, HC, mid arm circumference, SBP, DBP, and pulse (two BP readings will be taken with minimum of 3 min gap).
- Assess eligibility as per the trial inclusion and exclusion criteria.
- Arrange laboratory investigations, including pregnancy, if applicable. The laboratory investigations
  - Lipid profile (total cholesterol, HDL, LDL and triglycerides)
  - FBS and HbA1c
  - Liver profile (ALT, AST, AP)
  - Renal profile (Serum creatinine, ACR, Electrolytes-Na, K, Cl, eGFR) will be performed for all the participants.

If the patient fulfils the eligibility criteria he or she can be randomized on the same day or can randomize within one week.

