#### 4.4.2 Randomization

The subjects will be allocated to either cinnamon intervention or placebo group with an allocation ratio of 1:1 using random allocation sequence generated by the R software 'blockrand' package

[30]. Allocation concealment will be done by using pre-packed sequentially numbered containers for each patient. All the containers having the study drug, or the placebo will be identical in appearance with similar looking capsules, equal in weight and tamper– proof. Six bottles (each bottle with 35 capsules) with same code will be prepared for each patient for the treatment period and will be given sequentially. The investigators and participants will remain blinded to treatment allocation until the outcomes is analysed. The participants will be enrolled, assigned to the intervention and followed up throughout the study by the clinical team.

Post randomization, the participants will be assigned to either the cinnamon intervention group (1000 mg/daily) or the placebo group (Wheat flour -white colour tasteless odourless fine powder- 1000mg/daily) receiving the intervention in the form of capsules for 12 weeks. Each subject in both groups will be instructed to consume one capsules (500 mg) before breakfast and one capsule (500 mg) before dinner as well as continue with the diet and physical activity recommended to them by the investigator. The investigator may prescribe the same dose to be taken after meals (after breakfast and after dinner) if a participant shows any sign of intolerance due to taking the capsule before meals.

Weight, WC, HC, mid arm circumference, HbA1c, liver profile (AST, ALT and AP), serum creatinine level, ACR, electrolytes-Na, K, Cl, eGFR, SBP, DBP and pulse will be assessed before and after the intervention. Two cinnamon or placebo capsule bottles will be given every 4 weeks to the participants of the respective groups on their monthly visit to the clinic. Compliance to the protocol will be monitored in each visit. Participants will be advised to bring back the empty bottles with the left-over capsules (if any) at the time of the monthly visit to the clinic.

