#### Steps to be followed at Randomization (Visit 2)

- Record any AEs that have occurred since the screening visit (if randomization is done in a separate date).
- Perform pregnancy test & contraception review if applicable. If the participant is positive, then terminate the participant without randomization.
- Measure SBP, DBP and pulse (two BP readings will be taken with minimum of 3 min gap)
- Anthropometric measurements – Weight / WC / HC / mid arm circumference
- Review and record all medications currently being taken by the participant.

- Laboratory results obtained at screening will be considered as Baseline results – Lipid profiles done up to 7 days prior to screening visit will be considered to determine the eligibility at screening and as baseline lipid parameters.
- 
- Confirm that participant is suitable to be randomized.
- Randomize participant.
- Prescribe treatment according to group allocation.
- Two weeks of post randomization a compulsory follow up call will be given to all the participants.

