### 5.1 Formulation

The raw material (cinnamon bark) used in the production had been authenticated by the Industrial Technology Institute, Sri Lanka (ITI; Report No: CTS1715632). Fresh powdered cinnamon feed with particle size distribution ranging from 250  $\mu\text{m}$  to 1 mm is fed to the extractor. Extraction is carried out multiple times with aqueous + ethanol solvent to ensure the recovery of the maximum content of active compounds. Once water and ethanol solvent are evaporated mixture is passed through an ethanol recovery unit for recovery of ethanol. Then the concentrated output is passed through a vacuum dryer at specific temperatures to obtain a powder (with minimum of 15% proanthocyanidins (PAC A). Finally, 500mg of this powder is packed into size 0 capsules. The capsule preparation was carried out at a manufacturing site with GMP (Good Manufacturing Practices) certification.

The placebo capsule will contain pharmaceutical grade wheat flour (tasteless, odourless white colour fine powder). The placebo oral capsule will be identical in shape, size, weight and texture to the *C. zeylanicum* oral capsule. In order to mask the aroma, cinnamon quills would be put into packets containing both the placebo and cinnamon capsules.

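### The allergy exclusion names cinnamon only, although the placebo is wheat flour, so known wheat allergy or coeliac disease is kept out only by a general history and investigator judgement

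*Protocol*

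**What the plan says.** Section 3.2 of the Protocol lists "Participants with an allergy to cinnamon" as an exclusion, and the key exclusion criteria in the synopsis use the same words. No other allergy is named.

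The other capsule is described in two places. Section 5.1 says "The placebo capsule will contain pharmaceutical grade wheat flour". Section 4.4.2 gives the dose for the "placebo group (Wheat flour -white colour tasteless odourless fine powder- 1000mg/daily", taken for 12 weeks, with 1:1 allocation. On supply, the same section says "Six bottles (each bottle with 35 capsules) with same code will be prepared for each patient".

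Several steps could keep a wheat-sensitive person out:

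- Section 4.4.1: "Those who consent will be screened for eligibility into the study with Screening Form".
- Visit 1 steps: "Collect information on medical history", followed by an eligibility assessment.
- Section 3.2: a general clause that begins "Any condition that, in the opinion of the primary investigator" and covers anything that would contraindicate taking part.
- Visit 2 steps: "Confirm that participant is suitable to be randomized".

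Wheat allergy, gluten intolerance and coeliac disease are not mentioned in the criteria, the visit steps, the risk/benefit section or the safety section.

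**The concern.** When an allergy exclusion protects participants from the study product, it should cover everything they may be given. Each enrolled person here has a one-in-two chance of receiving wheat flour, and neither the participant nor the investigator will know. Yet the named exclusion addresses only the active capsule.

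Section 3.2 does not leave every foreseeable problem to the general clause. Cinnamon allergy and epilepsy each have their own line. A known contraindication to the placebo's only stated content deserves the same treatment.

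What is at stake is avoidable harm to an occasional placebo participant. Later steps are weaker protection, because they act only after exposure. Section 4.8 allows discontinuation for inability to tolerate. For intolerance linked to taking the capsule before meals, section 4.4.2 lets the investigator move the same dose to after meals, which would continue the exposure of someone reacting to wheat.

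**Working it through.** The plan states no figure on this point, so there is none to reproduce. The finding rests on the text, and the arithmetic only gives a sense of scale.

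**Criterion against content**

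| Capsule | Content (sections 4.4.2, 5.1) | Named allergy exclusion (section 3.2, synopsis) |
|---|---|---|
| Active | Cinnamon bark extract | Yes |
| Placebo | Wheat flour | No |

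**Wheat flour per placebo participant, full dosing**

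Inputs: two 500 mg capsules a day for 12 weeks, and six bottles of 35 capsules (section 4.4.2); Visit 5 at day 90, plus up to 5 days (section 4.7, Table 1); a follow-up call two weeks after randomization (Visit 2 steps).

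- 12 weeks: 2 × 0.5 g × 84 days = 84 g.
- To Visit 5: 1 g × 90 = 90 g, up to 1 g × 95 = 95 g.
- Supplied: 6 × 35 = 210 capsules, and 210 × 0.5 g = 105 g. This is a ceiling on supply, not an expected intake.
- To the two-week call: 1 g × 14 = 14 g.

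**Illustrative chance of exposure**

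Let p be the share of otherwise eligible adults with a known wheat allergy or diagnosed coeliac disease, and m the share of them missed by every check. The documents give neither. Assume p from 0.1% to 1%, and m of 1 (no check works), 0.5 or 0.2. With 75 placebo participants (section 8.1):

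- expected number exposed = 75 × p × m
- chance of at least one = 1 − (1 − p × m)^75

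| p | m = 1 | m = 0.5 | m = 0.2 |
|---|---|---|---|
| 0.1% | 0.075; 7.2% | 0.0375; 3.7% | 0.015; 1.5% |
| 0.5% | 0.375; 31.3% | 0.1875; 17.1% | 0.075; 7.2% |
| 1% | 0.75; 52.9% | 0.375; 31.3% | 0.15; 13.9% |

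For example, with p = 1% and m = 0.2: 75 × 0.01 × 0.2 = 0.15, and 1 − 0.998^75 = 13.9%.

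**Effect on the adverse-event comparison**

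Even if every affected person were missed and every one reacted, the placebo event rate would rise by p, that is, by 0.1 to 1.0 percentage points. With the checks working it would rise by less.

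**The case against.** The strongest reply is that section 3.2 is neither false nor contradictory, and that the general clause already covers the case. Meeting any listed criterion bars enrolment, and one criterion is any condition the investigator considers a contraindication. The same protocol tells investigators that the placebo is wheat flour. A diagnosed wheat allergy set against a wheat capsule is not a close call. Visit 1 takes a history and Visit 2 checks suitability again. The Screening Form, case record form and participant information are not available here. They may ask about food allergy, or disclose the wheat content so that an affected person declines.

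Much of this stands, and it rules out two inferences that a reader might draw. One is that the protocol admits wheat-allergic people unchecked. It does not, because the general clause excludes them once it is applied. The other is that exposure is about as likely as not. The 52.9% in the table needs both the highest assumed prevalence and the failure of every check for a condition the person already knows about, and nothing in the documents supports that.

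The gram totals also overstate exposure for the people of concern. Someone who reacts would not be expected to finish the course, and the two-week call and the monthly adverse-event reviews limit cumulative exposure.

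What remains is that none of the described steps names wheat. Exclusion depends on an open history eliciting the condition and on the investigator linking it to the placebo filler. Disclosure in the participant information would help, but it is not an eligibility criterion.

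**Conclusion.** The point holds as a narrow one about the wording of a criterion. The named allergy exclusion covers one capsule of two, and a known contraindication to the other is left to a general history and to discretion. It is a minor, low-probability but preventable participant-safety gap.

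The textual gap does not depend on any assumed figure. Its practical size does, because both the prevalence and the share caught are assumptions. If the existing checks catch 80%, the chance of at least one exposed placebo participant is about 1.5% to 14%; if they catch half, about 4% to 31%.

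A reader might infer that wheat reactions would bias the trial's results. The documents do not support that. The LDL endpoint, power and sample size are untouched, and the possible shift in the side-effect comparison is negligible.

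**What to change.** In section 3.2 and in the synopsis, reword the exclusion to *known allergy to cinnamon or wheat, or diagnosed coeliac disease*, and ask about it in the Visit 1 medical history. Limiting the wording to known allergy and diagnosed disease is deliberate. Self-reported gluten intolerance is a broader group, and the cost estimate below does not cover it.

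The cost is one line in two places and one screening question, with no change to the design or analysis. If 0.1% to 1% of otherwise eligible people have such a diagnosis (an assumption), the loss is 150 × 0.001 = 0.15 to 150 × 0.01 = 1.5 people, who can be replaced in recruitment.

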## 4. STUDY DESIGN

### 4.1 Study design and setting

The study will be a randomized, double-blinded, placebo-controlled clinical trial. It will be conducted at several hospitals in Sri Lanka for a period of 3 months, assessing the effects of the daily supplementation of capsules containing *C. zeylanicum* in individuals with average LDL level between 100-190 mg/dL ( $100 \text{ mg/dL} \leq \text{LDL} < 190 \text{ mg/dL}$ ). The duration of the trial will be 3 months, based on the evidence from previous research conducted on *C. zeylanicum*, and this duration is expected to be sufficient to identify changes in the primary outcome ( LDL level) assessed during the clinical trial.

### 4.2 Primary and secondary endpoints

#### **Primary endpoint**

The primary endpoint is:

- Reduction in LDL levels after three months of treatment.

#### **Secondary endpoint**

- Reduction in total cholesterol and triglycerides and/or effect on HDL levels
- Effect on serum glucose level related parameters (FBS, HbA1c)
- Effect on anthropometric parameters (weight, WC, HC, mid arm circumference)
- Effect on systolic and diastolic blood pressure.
- Occurrence of adverse events due to regular administration of *C. zeylanicum* extracts on liver and kidney function and the occurrence of self-reported side effects in individuals under study.

### 4.3 Outcome measurement

Outcomes of the study will be assessed at the end of the 3 months of the study. Anthropometric measures, SBP, DBP, FBS, serum lipids, serum creatinine, eGFR, albumin creatinine ratio (ACR) and liver profile (ALT, AST, AP) will be assessed at Visit 05. Drug compliance and any reasons for withdrawal from the study will also be recorded.

#### **Primary effectiveness measures**

- Change in LDL levels from baseline to final follow-up at three months post randomization.

#### **Secondary effectiveness measures**

- Changes in other lipid profile parameters (HDL, total cholesterol and Triglycerides)
- Changes in FBS and HbA1c
- Changes in anthropometric parameters
- Change in SBP and DBP.
- Potential effects of regular administration of *C. zeylanicum* extracts on liver and kidney function and the occurrence of self-reported side effects in participants of the study.

### 4.4 Visit details

#### 4.4.1 Screening

Adult volunteers aged between 18 - 70 years who are not on lipid lowering drugs will be screened for eligibility criteria after obtaining their consent. Informed consent will be obtained from all the participants for participation in the study. The participants will be required to sign or print thumb impression (those unable to sign). Those who consent will be screened for eligibility into the study with Screening Form. Individuals with average serum LDL level 100-190mg/dL will be recruited to the study considering other exclusion criteria and a unique study identifier will be given, and baseline data collection will be administered. All women of child-bearing potential must have a

negative highly sensitive pregnancy test 7 days or fewer before starting medication and must use a highly effective method of contraception throughout their participation in the study. Laboratory investigations will be conducted for the participants who are willing to participate in the study. Lipid profiles done up to 7 days prior to screening visit will be considered to determine the eligibility at screening and as baseline lipid parameters.

#### Steps to be followed at screening (Visit 1)

- Assess the potential participant's interest and eligibility for the trial.
- Discuss the trial with the participant, including using the participant information sheet, and obtain signed informed consent. This can also be done before the screening visit.
- Perform pregnancy test & contraception review if applicable
- Collect demographic information.
- Collect information on medical history
- Measure height, weight, WC, HC, mid arm circumference, SBP, DBP, and pulse (two BP readings will be taken with minimum of 3 min gap).
- Assess eligibility as per the trial inclusion and exclusion criteria.
- Arrange laboratory investigations, including pregnancy, if applicable. The laboratory investigations
  - Lipid profile (total cholesterol, HDL, LDL and triglycerides)
  - FBS and HbA1c
  - Liver profile (ALT, AST, AP)
  - Renal profile (Serum creatinine, ACR, Electrolytes-Na, K, Cl, eGFR) will be performed for all the participants.

If the patient fulfils the eligibility criteria he or she can be randomized on the same day or can randomize within one week.

#### 4.4.2 Randomization

The subjects will be allocated to either cinnamon intervention or placebo group with an allocation ratio of 1:1 using random allocation sequence generated by the R software 'blockrand' package

[30]. Allocation concealment will be done by using pre-packed sequentially numbered containers for each patient. All the containers having the study drug, or the placebo will be identical in appearance with similar looking capsules, equal in weight and tamper– proof. Six bottles (each bottle with 35 capsules) with same code will be prepared for each patient for the treatment period and will be given sequentially. The investigators and participants will remain blinded to treatment allocation until the outcomes is analysed. The participants will be enrolled, assigned to the intervention and followed up throughout the study by the clinical team.

Post randomization, the participants will be assigned to either the cinnamon intervention group (1000 mg/daily) or the placebo group (Wheat flour -white colour tasteless odourless fine powder- 1000mg/daily) receiving the intervention in the form of capsules for 12 weeks. Each subject in both groups will be instructed to consume one capsules (500 mg) before breakfast and one capsule (500 mg) before dinner as well as continue with the diet and physical activity recommended to them by the investigator. The investigator may prescribe the same dose to be taken after meals (after breakfast and after dinner) if a participant shows any sign of intolerance due to taking the capsule before meals.

Weight, WC, HC, mid arm circumference, HbA1c, liver profile (AST, ALT and AP), serum creatinine level, ACR, electrolytes-Na, K, Cl, eGFR, SBP, DBP and pulse will be assessed before and after the intervention. Two cinnamon or placebo capsule bottles will be given every 4 weeks to the participants of the respective groups on their monthly visit to the clinic. Compliance to the protocol will be monitored in each visit. Participants will be advised to bring back the empty bottles with the left-over capsules (if any) at the time of the monthly visit to the clinic.

#### Steps to be followed at Randomization (Visit 2)

- Record any AEs that have occurred since the screening visit (if randomization is done in a separate date).
- Perform pregnancy test & contraception review if applicable. If the participant is positive, then terminate the participant without randomization.
- Measure SBP, DBP and pulse (two BP readings will be taken with minimum of 3 min gap)
- Anthropometric measurements – Weight / WC / HC / mid arm circumference
- Review and record all medications currently being taken by the participant.

- Laboratory results obtained at screening will be considered as Baseline results – Lipid profiles done up to 7 days prior to screening visit will be considered to determine the eligibility at screening and as baseline lipid parameters.
- 
- Confirm that participant is suitable to be randomized.
- Randomize participant.
- Prescribe treatment according to group allocation.
- Two weeks of post randomization a compulsory follow up call will be given to all the participants.

